**S2 Trial protocol for ethics application**

| Synopsis |  |
| --- | --- |
| **Name of the Funding Source:** TBC | **Protocol Number:** ACTRN12621000426886p |
| **Study Title:** Feasibility and therapeutic efficacy of a two-week low-level laser acupuncture therapy for shoulder and neck pain in office workers: a pilot, single-blind, double-armed, randomised controlled trial | |
| **Short Title:** LLLA therapy for shoulder and neck pain | |
| **Planned Study Sites:** Perth, Australia | |
| **Number of Participants:** Seventy office worker aged 18-65, working more than 28 h a week with sedentary office work and have moderate to severe SNP (VAS > 5/10 & SF-MPQ >2/45) for more than three months will be recruited for the study | |
| **Chief Investigator:**  [name]  School of Nursing and Midwifery  Edith Cowan University  Western Australia, 6027 | |
| **Study Period:** December 2021 – December 2022 | |
| **Objectives:**  The primary objective of this study is to evaluate the feasibility of two weeks low-level laser acupuncture (LLLA) for office workers with shoulder and neck pain (SNP).  The secondary objective is to evaluate the therapeutic efficacy of LLLA on pain, work productivity and activity, and quality of life in office workers with SNP. | |
| **Study Design:** This study is a single-blind (assessors blind to group allocation), double-armed, randomised controlled trial. | |
| **Study Criteria:** office workers with SNP will be recruited for this study.  Inclusion criteria:   1. Aged between 18-65 years 2. Working more than 28 h a week with sedentary office work 3. Moderate to severe SNP (VAS > 5/10 & SF-MPQ > 2/45) for more than three months   Exclusion Criteria:   1. With a serious health conditions of the neck and shoulder 2. Pregnant 3. With cancer 4. High sensitivity to light | |
| **Sample Size:** Based on previous LLLA therapy intervention studies, n = 35 participants will be required per group (total n=70) for this study. | |

# Research Scope, Aims, Themes, Questions and Methods

**Aims or Questions**

The overarching aim of this study is to provide compelling evidence of the feasibility and therapeutic efficacy of (low-level laser acupuncture LLLA) for office workers with shoulder and neck pain (SNP).

**Benefit of exploring these research questions**

Several studies demonstrated that LLLA is a promising modality in pain management. However, there is no consolidated evidence for LLLA in managing shoulders and neck pain, and more studies in this field are required to provide updated evidence. Therefore, this study aims to address this knowledge gap. We anticipate, based on past research, the LLLA we will provide may be helpful in reducing levels of SNP. We hope that the results of our research can be used to inform our knowledge about how to better manage SNP that many office workers are suffering. There are no foreseeable risks associated with this research project.

**Outline the design of this research; its methods and details of the instruments to be used to collect the data, including psychometric properties if applicable.**

**Study design:**

This is a single-blind (assessors blind to group allocation), double-armed, randomised controlled trial on the feasibility and therapeutic efficacy of a two-week LLLA therapy for office workers with SNP.

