**Intervention group:**

In addition to usual care, participants will receive LLLA from a licensed acupuncturist at ECU Acupuncture Research Clinic. 10-20 minutes per session, three times a week for two weeks. The parameters of 3B Laser Pen (200mW) used for the intervention are wavelength of 808 nm in continuous wave mode, each pressure point receives 20 seconds of energy (4J) with 5 minutes being the maximum treatment time (60 J). At the end of two weeks receiving the therapy, participants will receive an online link to complete the post-intervention questionnaires.

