**Control group:**

Non-intervention but usual care

Participants in this group will be informed via email that they are in the no treatment group but will be emailed an online link to complete the post-intervention questionnaire in two weeks’ time.

Participates in the non intervention group will receive a complementary LLLA after the two weeks trial.

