**Secondary outcomes:**

The questionnaires used in this project to assess the outcomes including demographics data, VAS, SF-MPQ, WPAI:SHP, SF-12, and the participants’ motivation, challenges, and attitude of participating the trial. As a feasibility study, questions on non-pharmacologic therapy and out-of-pocket (OOP) expenses will also be included.

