**Psychological Risks**

Participants in the Non treatment group may feel disappointed. They will receive a complementary LLLA treatment after the two weeks trial as our appreciation and acknowledgement of their time.

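### The trial is labelled single-blind through blinded assessors, but every post-treatment efficacy outcome is self-rated online by participants who know their arm

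*Protocol*

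**What the plan says.** - **Label.** The Study design section reads "This is a single-blind (assessors blind to group allocation), double-armed, randomised controlled trial". The synopsis has the same: "This study is a single-blind (assessors blind to group allocation), double-armed, randomised controlled trial". PICOs repeats it, and the study title carries the word single-blind without the explanation in brackets. Blinded assessors are the only ground given for the label.
- **Outcomes.** Secondary outcomes lists the efficacy instruments: "The questionnaires used in this project to assess the outcomes including demographics data, VAS, SF-MPQ, WPAI:SHP, SF-12". They cover the efficacy domains of the secondary objective: pain, work productivity and activity, and quality of life.
- **LLLA arm.** Under Intervention group, "participants will receive LLLA from a licensed acupuncturist at ECU Acupuncture Research Clinic". After two weeks these participants are sent an online link to the post-intervention questionnaires.
- **Control arm.** Under Control group, the comparator is "Non-intervention but usual care", with no sham. The next sentence covers both disclosure and data collection: "Participants in this group will be informed via email that they are in the no treatment group but will be emailed an online link".
- **Order of events.** The section on formal recruitment puts the baseline survey before random allocation.
- **Expected reaction.** Psychological Risks says: "Participants in the Non treatment group may feel disappointed".

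**The concern.** Assessor blinding protects an outcome only when someone other than the participant, unaware of the arm, makes the rating. Here the participant makes the rating and knows the arm. The label therefore credits the efficacy results with a safeguard that the protocol's own data collection does not provide.

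Randomisation balances the arms at baseline. It does not prevent expectation, practitioner contact or disappointment from moving self-ratings after allocation. A between-arm difference in pain or quality of life would mix any laser effect with these influences. This matters because the aims section seeks strong evidence of therapeutic efficacy as well as feasibility. An ethics committee, or a reader of the eventual report, would take the single-blind label as support for that evidence.

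**Working it through.** **Step 1: who rates each efficacy outcome after treatment, and what the rater knows**

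| Instrument | Rater | Mode | Rater knows the arm? | Blinded assessor described? |
|---|---|---|---|---|
| VAS | Participant | Online link | Yes | No |
| SF-MPQ | Participant | Online link | Yes | No |
| WPAI:SHP | Participant | Online link | Yes | No |
| SF-12 | Participant | Online link | Yes | No |

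The instruments come from Secondary outcomes, and the mode from Intervention group, Control group and the formal recruitment section. Knowledge of the arm follows from six clinic sessions in one arm and the email in the other. Result: 4 of 4 instruments are rated by unblinded participants and 0 of 4 by a blinded assessor. The protocol describes no objective or rater-administered efficacy measure.

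**Step 2: what this does not cover**

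- Baseline ratings precede allocation, so they are made before the arm is known.
- Recruitment, completion and adherence are counts.
- For adverse event severity the protocol names no rater; a blinded one is neither described nor excluded.

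**Step 3: the planned sample size, to fix n for an illustration**

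Study population gives 30 per group, 15% attrition and 35 per group. Inflating: 30 × 1.15 = 34.5, rounded up to 35; or 30 / 0.85 = 35.3, rounded up to 36. The stated 35 is reproduced to within one participant. Expected completers: 35 × 0.85 = 29.75, about 30 per arm. The point about blinding does not depend on this figure.

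**Step 4: illustration of what a reporting shift could do**

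The documents give no size for such a shift, so a range is assumed. Inputs: n = 30 per arm, two-sided two-sample t-test, 58 degrees of freedom, no laser effect, shift b in SD units. The noncentrality is b × √(30/2) = b × 3.873. The critical value is 2.002 at alpha 0.05. The protocol plans an unspecified correction for multiple comparisons. As a second assumption, Bonferroni over four instruments gives 0.05/4 = 0.0125 and a critical value of 2.578.

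| Assumed shift b (SD) | Noncentrality | Significant at 0.05 | Significant at 0.0125, per outcome |
|---|---|---|---|
| 0 | 0 | 5% | 1.25% |
| 0.1 | 0.387 | 6.7% | 1.9% |
| 0.2 | 0.775 | 11.9% | 4.1% |
| 0.3 | 1.162 | 20.8% | 8.6% |
| 0.5 | 1.936 | 47.8% | 27.0% |

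The planned analysis is a repeated measures ANOVA, possibly adjusted for baseline, so the exact figures could move either way.

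**The case against.** The strongest reply is that this is a pilot with feasibility primary. A usual-care comparator is a legitimate and openly stated choice, and the label changes neither the sample size, the analysis nor the primary outcome. All of that stands. It limits the consequence to the secondary efficacy inference, but it does not make the label true.

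The illustration is also open to attack. The shifts are assumed, and small ones do little harm. The planned correction lowers the per-outcome rates. Part of the attention and expectation effect belongs to the package that is being compared with usual care, so not every such rejection is a false positive. This stands too, and the figures should be read only as a range.

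Three stronger readings are tempting, and the protocol does not support them:

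- *That no outcome at all is assessed blind.* Baseline ratings are given before allocation, and a blinded rater for adverse event severity is not excluded.
- *That the control email contradicts the comparator.* It says "Participants in this group will be informed via email that they are in the no treatment group", but directly beneath "Non-intervention but usual care", and the formal recruitment section likewise pairs no treatment with usual care. The natural meaning is no study treatment on top of usual care. The protocol describes the email without giving its text.
- *That the email increases the disappointment in the control arm.* Psychological Risks does not link the two, and it offers complementary LLLA afterwards.

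Nor could the label be rescued by a blinded statistician. The protocol mentions none, and blinding the analysis would not blind the ratings.

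**Conclusion.** The point holds for the post-treatment efficacy outcomes. The protocol rests its single-blind label on blinded assessors, describes none, and collects all four efficacy instruments from participants who know their arm. This follows from the text alone and needs no numerical assumption.

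The size of any bias is unknown. Under an assumed shift of 0.1 to 0.5 SD, with 30 per arm and no laser effect, the chance of a significant result would be about 7% to 48% at an unadjusted two-sided 0.05. With Bonferroni over four outcomes, also an assumption, it would be about 2% to 27% per outcome against a nominal 1.25%. The effect falls on the secondary efficacy claim; the primary feasibility objective is largely untouched.

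**What to change.** - Remove single-blind from the study title, and remove the label with its bracketed ground from the synopsis, Study design and PICOs.
- Describe the trial as open-label with participant-reported efficacy outcomes.
- State that the secondary efficacy contrast is LLLA plus clinic contact added to usual care, against usual care alone. It cannot separate a laser effect from expectation and attention.
- Bring the efficacy claim in the aims section into line with that limit.
- If a size for the possible bias is quoted, mark it as an assumption and show the full range.

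Neutral wording of the control-arm email is optional; the present description is not an error, and rewording would not blind anyone. The change costs only text, with no effect on sample size or procedures. The downside is a less favourable design label and a narrower efficacy claim.

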**Study type:**

Interventional study

**PICOs:**

P: Office worker aged 18-65, working more than 28 h a week with sedentary office work and have moderate to severe SNP (VAS > 5/10 & SF-MPQ >2/45) for more than three months will be recruited for this trial

I: LLLA + usual care

C: Usual care

O:

The primary objective of this study is to evaluate the feasibility of two-week LLLA for office workers with SNP.

The secondary objective is to evaluate the therapeutic efficacy of LLLA on pain, work productivity and activity, and quality of life in office workers with SNP.

S: This is a single-blind (assessors blind to group allocation), double-armed, randomised controlled trial on the feasibility and therapeutic efficacy of a two-week LLLA therapy for office workers with SNP.

**Intervention and exposure:**

The study will involve providing participants with LLLA to managing SNP.

All potential participants will be provided with an online information sheet and consent form outlining what will be involved in the trial. People who gave consent will complete the online survey after their signed the consent form.

 To reduce certain sources of bias when testing the efficacy of LLLA; this is accomplished by randomly allocating participants to two groups, one group that provides treatment and the other without treatment, and then comparing them with respect to a measured response. This is to provide the most reliable evidence on the efficacy of interventions because the processes used during an RCT minimise the risk of confounding factors influencing the results.

Participants will then be randomised to one of the two groups.

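### The two arms can estimate the effect of adding an LLLA visit programme to usual care; the stated aim, secondary objective and rationale claim more than that

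*Protocol*

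**What the plan says.** **The contrast.** The PICOs section of the Protocol defines the experimental arm as "I: LLLA + usual care" and the comparator as usual care.

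- *LLLA arm.* The Intervention group section gives "10-20 minutes per session, three times a week for two weeks", delivered by a licensed acupuncturist at a clinic, "with 5 minutes being the maximum treatment time (60 J"). The section on formal recruitment confirms six sessions.
- *Control arm.* The Control group section gives "Non-intervention but usual care". It adds: "Participants in this group will be informed via email that they are in the no treatment group". These participants are sent the follow-up questionnaire link by email two weeks later. Afterwards, "Participates in the non intervention group will receive a complementary LLLA after the two weeks trial".

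**Blinding and outcomes.** The Synopsis, Study design and PICOs sections describe only the assessors as blind. VAS, SF-MPQ, WPAI:SHP and SF-12 are questionnaires (Secondary outcomes) that participants reach through an online link.

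**The claim.** The Synopsis and PICOs state the objective: "The secondary objective is to evaluate the therapeutic efficacy of LLLA on pain, work productivity and activity, and quality of life". Aims or Questions goes further and promises compelling evidence of efficacy. Intervention and exposure supports this by appeal to randomisation: "This is to provide the most reliable evidence on the efficacy of interventions because the processes used during an RCT minimise the risk of confounding" (the sentence goes on to refer to such factors influencing the results).

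**The concern.** The arms differ in more than the laser. Those allocated to LLLA also receive clinic attendance, one practitioner's attention six times, and the expectation that follows from knowing they are treated. Those allocated to control are told that they are untreated, and the Psychological Risks section itself foresees disappointment among them. All of these follow from allocation, so they are not confounders in the sense that randomisation controls.

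The rationale in Intervention and exposure treats control of confounding as enough to make the comparison a reliable test of LLLA efficacy. If the report follows that wording, a significant difference in any of the four questionnaires would be published as therapeutic efficacy of LLLA. What the trial would have shown is that the laser and its visits, taken together and added to usual care, changed what participants reported. A later trial or a clinical reader could then credit the laser with an effect that this design cannot assign to it.

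**Working it through.** **1. The plan's own figures.** The Intervention group section gives 200 mW, 20 seconds and 4 J per point, and a maximum of 5 minutes and 60 J.

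- Per point: 0.2 W × 20 s = 4 J.
- Maximum: 0.2 W × 300 s = 60 J.

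Both reproduce. No sample-size figure bears on this point, and the protocol gives no effect size, SD or power.

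**2. What each arm receives from the trial during the two weeks.**

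| Component | LLLA arm | Control arm |
|---|---|---|
| Usual care | yes | yes |
| Laser | yes | no |
| Trial visits | 3 per week × 2 weeks = 6 | none |
| Visit time | 6 × 10 to 20 min = 60 to 120 min | none from the trial |
| Knows allocation | yes | yes, told by email |
| Questionnaire link | yes | yes |

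The content of usual care, and any practitioner time within it, is not quantified. The control entries therefore concern trial visits only. If the 5-minute cap applies per session (the natural reading, but an assumption), laser time is at most 6 × 5 = 30 min. Some of each visit is then not irradiation. That shows an unmatched component exists; it does not measure its effect.

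**3. What the difference estimates.** For simplicity, assume that effects add. Let U be the expected outcome under usual care, L the laser effect, V the effect of visits and attention, E the effect of expecting benefit, and D the effect of disappointment among controls, all signed so that positive values favour LLLA.

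- LLLA arm mean: U + L + V + E
- Control arm mean: U − D
- Difference: L + V + E + D

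Randomisation makes U the same in both arms in expectation, and it does nothing more. Two arms yield one contrast, so L cannot be recovered from the sum. Having a blinded assessor rate the outcomes would not remove V, because the visits themselves are unmatched.

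**4. Illustration on assumed values.** None of the effect sizes below is in the protocol. Set L = 0 and let V + E + D equal d SD. Take 30 analysed per arm, which is the base number in Study population and close to 35 × 0.85 = 29.75. Use an unadjusted comparison of two means at two-sided 0.05, without multiplicity correction. (The protocol gives 0.05 without stating sidedness, and plans a correction, which would lower these chances.)

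| Assumed d (SD) | Chance of a significant result favouring LLLA |
|---|---|
| 0.2 | 12% |
| 0.3 | 21% |
| 0.4 | 34% |
| 0.5 | 49% |
| 0.6 | 64% |

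Each would be a correct finding about the programme and a wrong one about the laser.

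**The case against.** The best case for the protocol has four parts.

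- *The contrast is disclosed.* The PICOs section states the add-on comparison openly. This stands, and it is a reason to bring the objective and rationale into line with it.
- *LLLA may mean the delivered therapy.* No section explicitly claims an effect of irradiation apart from its delivery, and add-on versus usual care is a valid pragmatic question. This stands as a defence of the design. It does not rescue the promise of compelling efficacy evidence, or a rationale that relies on control of confounding without mentioning contact and expectation.
- *The rationale is broadly right about randomisation.* It speaks of reducing certain sources of bias, and it does not assert that contact effects vanish. That is fair. The fault is that it is offered as sufficient support for an efficacy claim.
- *This is a pilot.* Its primary objective is feasibility, and the comparator does no harm to recruitment, completion, safety or adherence. This stands and limits the consequence. Even so, the protocol also sets an efficacy objective and plans significance tests for it.

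A reader might go further in three ways that the documents do not support. First, that controls have no contact at all: they keep usual care, receive emails and a questionnaire, and are offered LLLA afterwards. Second, that the proportion of session time without laser measures the bias: minutes are not effect, and some of that time is needed to deliver treatment, for example to fit the safety eyewear that the Physical Risks section requires. Third, that the comparator is wrong and a sham arm is required: for a feasibility pilot with an add-on question, it is not.

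**Conclusion.** The point holds as a mismatch between claim and design. The comparison identifies the effect of adding a two-week LLLA programme, laser plus visits, to usual care. It cannot separate the laser effect from contact and expectation. The aim, the secondary objective and the rationale in Intervention and exposure claim more than that.

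This conclusion rests on the stated arms, on participants knowing their allocation, and on their completing the questionnaires themselves; it needs no outside figure. The size of the non-laser contribution is unknown and cannot be estimated from these two arms. The 12% to 64% range is illustrative and depends wholly on the assumed 0.2 to 0.6 SD. The correction is worth making because it changes what the trial may conclude on its secondary outcomes. It changes nothing about the primary outcome, the sample size or the analysis.

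**What to change.** 1. In the Synopsis and PICOs, restate the secondary objective as *the effect of adding a two-week LLLA programme to usual care, compared with usual care alone*, on the listed outcomes.
2. Bring the matching efficacy wording in Aims or Questions and Study design into line, and remove the promise of compelling evidence of efficacy.
3. In Intervention and exposure, say that randomisation balances baseline factors but that this comparator does not separate the laser from practitioner contact and expectation.
4. State that conclusions on the secondary outcomes will be limited to the add-on contrast.

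The cost is wording only: no new arm, visit, participant or analysis. The downside is a more modest claim. A laser-specific effect would need a comparator that matches the visits, such as a sham; that is a question for a later trial and not a condition of this one.

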**Intervention group:**

In addition to usual care, participants will receive LLLA from a licensed acupuncturist at ECU Acupuncture Research Clinic. 10-20 minutes per session, three times a week for two weeks. The parameters of 3B Laser Pen (200mW) used for the intervention are wavelength of 808 nm in continuous wave mode, each pressure point receives 20 seconds of energy (4J) with 5 minutes being the maximum treatment time (60 J). At the end of two weeks receiving the therapy, participants will receive an online link to complete the post-intervention questionnaires.

